## Abstract

**Background:**

The Transfusion Indication Threshold Reduction (TITRe2) trial is the largest randomized controlled trial to date to compare red blood cell transfusion strategies following cardiac surgery. This update presents the statistical analysis plan, detailing how the study will be analyzed and presented. The statistical analysis plan has been written following recommendations from the International Conference on Harmonisation of Technical Requirements for Registration of Pharmaceuticals for Human Use, prior to database lock and the final analysis of trial data. Outlined analyses are in line with the Consolidated Standards of Reporting Trials (CONSORT).

**Methods and design:**

The study aims to randomize 2000 patients from 17 UK centres. Patients are randomized to either a restrictive (transfuse if haemoglobin concentration <7.5 g/dl) or liberal (transfuse if haemoglobin concentration <9 g/dl) transfusion strategy. The primary outcome is a binary composite outcome of any serious infectious or ischaemic event in the first 3 months following randomization.

The statistical analysis plan details how non-adherence with the intervention, withdrawals from the study, and the study population will be derived and dealt with in the analysis. The planned analyses of the trial primary and secondary outcome measures are described in detail, including approaches taken to deal with multiple testing, model assumptions not being met and missing data. Details of planned subgroup and sensitivity analyses and pre-specified ancillary analyses are given, along with potential issues that have been identified with such analyses and possible approaches to overcome such issues.

**Trial registration:**

ISRCTN70923932.

## Update

This paper provides the detailed statistical analysis plan for the Transfusion Indication Threshold Reduction (TITRe2) randomized controlled trial, comparing transfusion rates, morbidity and healthcare resource use following two different transfusion strategies after cardiac surgery.

## Background

Perioperative anaemia is common after cardiac surgery, and transfusion of allogeneic red blood cells (RBCs) is the preferred treatment for acute anaemia. Observational studies suggest that transfusion is harmful after cardiac surgery [1-3]; by contrast, randomized controlled trials of restrictive (lower haemoglobin level) versus more liberal (higher haemoglobin level) RBC transfusion thresholds have not demonstrated adverse effects attributable to transfusion [4]. Uncertainty about a safe restrictive RBC transfusion threshold in cardiac surgery persists and is reflected in transfusion rates across cardiac centres ranging from 25 to 75% [5] in the UK and 8 to 93% [6] in the USA. The TITRe2 trial has been established to address the current uncertainty around safe haemoglobin levels for RBC transfusion after cardiac surgery.

## Methods and Design

TITRe2 is a multicentre, UK-wide, open parallel group randomized controlled trial. It is the largest randomized controlled trial to date (2,000 randomized patients) to compare RBC transfusion strategies following cardiac surgery. Patients are randomized in a 1:1 ratio to one of two RBC transfusion strategies: (a) a ‘restrictive’ threshold, whereby transfusions are given if the haemoglobin concentration is below 7.5 g/dl (or haematocrit <22%), or (b) a ‘liberal’ threshold, whereby transfusions are given if the haemoglobin concentration is below 9 g/dl (or haematocrit <27%). Cohort minimization is used to minimize imbalance of: (a) centre and (b) operation type. The study population is all adult patients (aged 16 or over) undergoing non-emergency elective cardiac surgery (this includes non-emergency cases admitted from home and non-emergency inpatient cases). Eligibility criteria are as inclusive as possible, to promote the applicability of the evidence obtained during the trial. Full details of the study background and design have been reported elsewhere [7].

Following recommendations from the International Conference on Harmonisation of Technical Requirements for Registration of Pharmaceuticals for Human Use [8], a pre-specified detailed statistical analysis plan has been written prior to database lock and final analysis of the trial data. However, during the course of the study, analysis requested by the Data Monitoring and Safety Committee has been performed prior to finalization of this statistical analysis plan. This analysis comprised monitoring of recruitment rates and data completeness, monitoring of demographic data, and descriptive comparisons of safety data, including the primary outcome measure, by masked treatment allocation. At a pre-planned interim analysis carried out after half the participants had been followed up, a formal comparison was performed for the primary outcome measure only. No formal comparisons were performed at any other time.

### Study objectives

The objectives of the randomized controlled trial are to: (a) estimate the difference in the risk of a postoperative infection or ischaemic event between restrictive and liberal transfusion thresholds; (b) compare the effects of restrictive and liberal transfusion thresholds with respect to a range of secondary outcomes; (c) estimate the cost-effectiveness of the restrictive compared with the liberal haemoglobin transfusion threshold and describe this in terms of a cost-effectiveness acceptability curve. A UK National Health Service Research Ethics Committee (Oxfordshire C) approved the study (08/H0606/125). The trial is registered (ISRCTN70923932).

### Outcomes

The primary outcome measure is a binary composite outcome of any serious infectious (sepsis or wound infection) or ischaemic (permanent stroke, myocardial infarction, acute kidney injury or gut infarction) event in the first 3 months after randomization. Full details of qualifying events and the manner in which they will be verified are available in the protocol [7].

Secondary outcome measures are:Units of RBCs and other blood components transfused during a participant’s hospital stay,Proportion of patients experiencing an infectious event,Proportion of patients experiencing an ischaemic event,EQ5D [9],Duration of postoperative stay in intensive care or high dependency unit,Duration of postoperative hospital stay,All-cause mortality,Significant pulmonary morbidity, comprising: (a) initiation of non-invasive ventilation (for example, continuous positive airway pressure ventilation), (b) reintubation/ventilation, or (c) tracheostomy,Cumulative resource use, cost and cost-effectiveness. (This analysis is being undertaken by the Health Economics Research Centre at the University of Oxford and is not covered in this statistical analysis plan.)

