**Flow of participants.**

Participants consent to the study before surgery if they meet all of the pre-consent eligibility criteria (see Figure 1) and give written consent. They are then randomized if at any point post-surgery they meet the post-consent eligibility criteria (haemoglobin concentration falls below 9 g/dl or haematocrit below 27%). This means that a significant proportion of patients (estimated to be approximately 30% from earlier studies [1]) consent to the study but are not randomized. Randomized patients should be given a RBC transfusion as soon as possible after haemoglobin or haematocrit levels breach the relevant thresholds, and at most within 24 hours.

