### Descriptive data

Pre-randomization characteristics (for example, patient demography, intra-operative details and pre-randomization RBC transfusions) will be described by treatment allocation for patients in the analysis population. Continuous variables will be summarized using the mean and standard deviation (or median and interquartile range if the distribution is skewed), and categorical data will be summarized as a number and percentage. Any imbalances in the characteristics of the patients will be described but statistical tests for imbalance will not be carried out in line with recommendations [10]. In addition, available characteristics will be described by: (a) non-consented and consented patients and (b) consented but not randomized (because threshold was not breached) and randomized patients (including pre- and intra-operative characteristics, transfusions, haemoglobin levels, EQ5D data and mortality).

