**Table 2 Tab2:** **Classification of primary and secondary outcomes**

**Category**	**Outcomes**
Binary outcome measures	• Primary outcome measure: proportion of patients experiencing an infectious or ischaemic event
	The following secondary outcome measures:
	• Proportion of patients experiencing an infectious event
	• Proportion of patients experiencing an ischaemic event
	• Use of activated factor seven
	• Use of Human Blood Coagulation Factor IX
	• Significant pulmonary morbidity
Continuous outcome measures	The following secondary outcome measures:
	• Units of RBCs transfused
	• Fresh frozen plasma transfusions
	• Cryoprecipitate transfusions
	• Platelet transfusions
Time-to-event outcome measures	The following secondary outcome measures:
	• Time from randomization to first occurrence of the primary outcome measure (secondary analysis of the primary outcome measure)
	• Duration of post-randomization stay in intensive care or high dependency unit
	• Duration of post-randomization hospital stay
	• Time from randomization to death from any cause
Continuous longitudinal outcome measures	The following secondary outcome measures:
	• EQ5D single summary index score
	• EQ5D visual analogue scale score

General presentation and analysis techniques for each type of outcome are described next.

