### Sensitivity analyses

The following sensitivity analyses have been identified; these were not pre-specified in the study protocol:Examining treatment estimates for the primary outcome by site, ordering sites by rates of severe non-adherence with the transfusion protocol: the hypothesis is that the treatment effect should tend towards the null with increasing non-adherence.Assessing the effect of the timing of primary outcome following randomization on the primary outcome by excluding all events that occurred in the first 24 hours after randomization: the hypothesis is that events in the first 24 hours are unlikely to be due to a post-randomization transfusion.Assessing the effect of the transfusions before randomization on the primary outcome by excluding patients who were transfused prior to randomization.Assessing the effect of acute kidney injury: acute kidney injury is defined according to the Acute Kidney Injury Network criteria [16] as either: (a) an increase in serum creatinine concentration (≥26.5 μmol/l, or ≥150% change from baseline) over a period of less than 48 hours, (b) restricted urine output (<0.5 ml/(kg h)) for more than 6 hours or (c) the need for renal replacement therapy. Highest daily creatinine levels are recorded separately from clinical judgment of acute kidney injury, so the following sensitivity analyses are planned to re-analyze the primary outcome: (a) excluding patients identified with acute kidney injury who do not have an increase in serum creatinine concentration over a 48 hour period or less, according to the daily highest creatinine concentration values collected, (b) including patients who have not been identified as having acute kidney injury, but according to the daily highest creatinine concentration data have a rise in serum creatinine concentration that would meet the criteria (and who were not having haemofiltration or dialysis pre-operatively).Serious primary outcome events: the pre-planned interim analysis after half the study participants had been recruited showed that the majority of the primary outcome events are either sepsis or acute kidney injury, and therefore the primary outcome will be re-analyzed including only the more ‘serious’ events. This will mean the following changes to the definition of the overall primary outcome: (a) all myocardial infarctions, gut infarctions and strokes will be included, (b) only the most severe acute kidney injury cases (stage 3) will be included, (c) all wound infections identified via asepsis scoring will be excluded (the more serious wound infections will be identified via serious sepsis events), (d) serious pre-discharge sepsis events will be identified by the presence of sepsis plus organ failure (defined as: myocardial infarction, stroke, acute kidney injury, laparotomy for gut infarction and one or more of reintubation, acute respiratory distress syndrome, low cardiac output or tracheostomy), (e) post-discharge sepsis events will be included, as they require hospitalization.

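### The transfused-units outcome runs over the whole hospital stay, so it counts units given before randomization; this costs precision and, on a log scale only, pulls the ratio modestly towards 1

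*SAP article*

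**What the plan says.** The Outcomes section gives the counting window: "Units of RBCs and other blood components transfused during a participant’s hospital stay". Table 2 lists "Units of RBCs transfused", and likewise plasma, cryoprecipitate and platelets, as continuous outcomes with no window. The same table anchors its neighbours to randomization: "Duration of post-randomization stay in intensive care or high dependency unit" and "Duration of post-randomization hospital stay". The Outcomes section calls both of these stays postoperative, and Table 3 still does so for the hospital stay.

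On the timing of allocation, the Flow of participants section says of consented patients: "They are then randomized if at any point post-surgery they meet the post-consent eligibility criteria". The criterion is a haemoglobin below 9 g/dl or a haematocrit below 27%.

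The plan recognises that blood is given before that point. Descriptive data includes "intra-operative details and pre-randomization RBC transfusions" among the characteristics to be tabulated by arm. One sensitivity analysis deals with it, for the primary outcome only: "Assessing the effect of the transfusions before randomization on the primary outcome by excluding patients who were transfused prior to randomization".

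The Continuous outcomes section reports a difference in means for untransformed data and a ratio of geometric means for log-transformed data. The Adjustment in models section adjusts for operation type and centre only.

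**The concern.** Allocation cannot influence a unit given before it. Units given in theatre, or after surgery but before the threshold is breached, still fall within the hospital stay and so enter this outcome. The plan therefore reports the same RBC units once as baseline and again inside an outcome, and nothing in the analysis removes or adjusts for them.

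This outcome is a direct measure of how far the two strategies separated in blood use. The Adherence section says that power falls if transfusion rates do not match the sample-size assumptions, so readers will want that separation measured cleanly. Units that carry no treatment effect add variance to the comparison. On a ratio scale they also add the same expected amount to both arms, which moves the ratio towards 1.

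**Working it through.** **The plan's own figure.** The article gives no mean, SD or target difference for transfused units. Its only sample-size figure concerns the primary outcome: 17% v 11%, 90% power, two-sided 5%, 1:1 allocation. The two-proportion formula gives 701 per arm (1,402) without continuity correction and 734 per arm with it. 2 × 734 = 1,468, exactly as stated. This point does not touch that calculation.

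**Inputs for this outcome.** Window, timing of randomization, effect measures and adjustment set come from the sections cited above. All unit means and SDs below are assumptions.

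**Step 1: difference in means.** Write the whole-stay count as pre + post. Randomization gives pre the same expectation in both arms, so

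E(difference, whole stay) = E(difference, post).

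There is no bias. For precision, let r = SD(pre)/SD(post), with pre and post independent:

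SE(whole stay)/SE(post) = √(1 + r²).

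- r = 0.5: √1.25 = 1.12, so the SE rises by 12%; effective sample size is 1/1.25 = 80%.
- r = 1.0: √2 = 1.41, so the SE rises by 41%; effective sample size is 1/2 = 50%.

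**Step 2: simulation with counts.** Over-dispersed counts were simulated with 400,000 patients per arm. Assumed post-randomization means were 2.0 (liberal) and 1.2 (restrictive), with assumed pre-randomization means of 0.25, 0.5 and 1.0. Pre-randomization counts were either independent of later ones or shared a patient-level tendency to bleed or be transfused (run for 0.5 and 1.0 only). z is for 1,000 per arm.

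| Pre mean | Link to post | Difference in means | SD, post → whole stay | Geometric-mean ratio (x+1), post → whole stay | z for difference, post → whole stay |
|---|---|---|---|---|---|
| 0.25 | independent | about −0.8 | 2.07 → 2.17 | 0.78 → 0.79 | 8.5 → 8.2 |
| 0.5 | independent | about −0.8 | 2.08 → 2.34 | 0.78 → 0.80 | 8.5 → 7.6 |
| 1.0 | independent | about −0.8 | 2.08 → 2.80 | 0.78 → 0.81 | 8.7 → 6.5 |
| 0.5 | shared | about −0.8 | 2.09 → 2.60 | 0.78 → 0.81 | 8.6 → 7.0 |
| 1.0 | shared | about −0.8 | 2.08 → 3.09 | 0.78 → 0.83 | 8.6 → 5.8 |

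With assumed means of 1.5 and 1.0, the difference stays at about −0.5, the SD rises from 1.7 to between 1.8 and 2.7, and the geometric-mean ratio moves from 0.84 to 0.85-0.88.

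**Step 3: reading.** The difference in means does not move. Its SD rises by about 5% (2.17/2.07) in the mildest case and by about 60% (2.71/1.69, means 1.5 and 1.0, shared tendency) in the strongest. The geometric-mean ratio shifts towards 1 by 0.01 to 0.05.

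**The case against.** The strongest reply is that total blood use per admission, compared by allocation, is a valid randomized comparison. The Update section names healthcare resource use among the things compared. On that view the whole-stay count is a choice of estimand, not an error. This stands in part: the whole-stay total deserves reporting, but as the treatment comparison it is less efficient and does not match the randomization-based durations beside it in Table 2.

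A second reply is that the outcome list is condensed and the protocol may set a narrower window. The protocol is not shown. But the article states a window rather than leaving it open, and Table 2 does not change it. The ancillary analyses do name both periods explicitly when they count RBC units. That suggests the authors distinguish the two periods, but it does not say which one applies here.

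Third, adherence is assessed separately from randomization to discharge, and pre-randomization RBC transfusions are tabulated by arm, so readers have other evidence on delivery. That is true and limits the harm.

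Several stronger readings are tempting but not supported:

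- *The separation in blood use will look smaller.* This is not so for the difference in means, which keeps its expectation.
- *The ratio is heavily diluted.* A ratio of arithmetic means would move more: with assumed means of 1.3 and 2.0, from 0.65 to (1.3 + 1.0)/(2.0 + 1.0) = 0.77 when one unit is added to each arm. The plan reports no such ratio; its only ratio is of geometric means, and only if data are log-transformed.
- *The standard error could rise by 80%.* That needs r = 1.5, for which the document gives no basis. Adjustment for operation type and centre may also absorb some of the added variance.
- *The Outcomes and Descriptive data sections contradict each other.* Units can be tabulated at baseline and also sit inside a total. The overlap is inefficient, not contradictory.

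**Conclusion.** The point holds as a matter of definition and precision in a secondary outcome. As written, the count includes units that allocation cannot affect, and the models neither remove nor adjust for them. The difference in means is unbiased; its SE rises by about 12% to 41% if r lies between 0.5 and 1.0 and the two counts are independent. A positive link between them would raise it further. On the log scale, the ratio of geometric means moves modestly towards 1, from about 0.78 to 0.79-0.83 on an x+1 scale with assumed post-randomization means of 2.0 and 1.2.

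All these sizes rest on assumed unit means and SDs. In every scenario run, z stayed above 4 with 1,000 per arm, so what suffers is the precision of the estimate, and on the log scale its size, rather than the ability to detect a difference. The primary outcome and its 1,468 are unaffected.

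**What to change.** - Define the RBC-units comparison as units from randomization to hospital discharge. This matches Table 2's durations and the period over which adherence is assessed.
- Report "pre-randomization RBC transfusions" as baseline, as already planned.
- Give the whole-stay total by arm as a descriptive resource-use line.
- Treat plasma, platelets and cryoprecipitate the same way where their timing relative to randomization was recorded. Elsewhere, keep the whole-stay count and label it as such.

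For RBCs this needs only wording and a re-cut of existing data, because judging adherence already requires the timing of RBC transfusions relative to randomization. The article gives no such evidence for the other components, so their timing must be checked first. The Discussion says that the plan has already been executed, so in practice the change bears on how the result is defined and reported, and should be labelled as made after the plan.

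A small downside is that the shorter window leaves more zero counts, for which a plain log transformation is undefined. The Continuous outcomes section already allows other methods, and Model assumptions names a two-part model that could serve.

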### Sample size

Based on previous data [1] and allowing for anticipated non-adherence to the allocated thresholds [7], the primary outcome frequencies were hypothesized to be 17% and 11% in the liberal and restrictive groups. A sample size of 1,468 was required to detect this difference with 90% power and 5% significance (two-sided test). The target sample size was inflated to 2,000 to allow for uncertainty about non-adherence, since higher than expected non-adherence would reduce power. Full details are reported elsewhere [7].

### Flow of participants

The flow of participants will be described using a flowchart (see Figure 1) as recommended by the Consolidated Standards of Reporting Trials (CONSORT) [10].

**Figure 1 Fig1:**
[figure not shown]
**Flow of participants.**

Participants consent to the study before surgery if they meet all of the pre-consent eligibility criteria (see Figure 1) and give written consent. They are then randomized if at any point post-surgery they meet the post-consent eligibility criteria (haemoglobin concentration falls below 9 g/dl or haematocrit below 27%). This means that a significant proportion of patients (estimated to be approximately 30% from earlier studies [1]) consent to the study but are not randomized. Randomized patients should be given a RBC transfusion as soon as possible after haemoglobin or haematocrit levels breach the relevant thresholds, and at most within 24 hours.

### Withdrawals

Patients can withdraw their consent for the study at any time; reasons for withdrawal are collected, along with instructions as to (a) whether data already collected can be used and (b) whether the patient is happy to participate in follow-up sessions. In addition, clinicians can choose to permanently discontinue treatment according to the protocol for a patient; this does not constitute a withdrawal and data collection continues as planned but transfusions need no longer be given according to the study protocol.

### Patient population

The analysis population will consist of all randomized patients, excluding: (a) patients marked as ‘randomized in error’ and (b) withdrawn patients who were unwilling for data collected to be used. Randomization in error is expected to happen rarely (<10 patients); it occurs when a member of research staff realizes shortly after randomization and prior to any intervention that a randomized participant is not in fact eligible. All study analyses will be performed on a modified intention-to-treat basis (including all randomized patients, with the exception of withdrawn patients or those with missing outcome data).

